### Participants

The study aims to include 100 patients with primary CD of 30 years and older, stable on BTX treatment for more than one year. Exclusion criteria are secondary or hereditary forms of dystonia, dystonia in other bodyparts than the neck and patients who had surgery for the treatment of dystonia.

### Interventions

#### Standardized, tailored PT program

Subjects in this group receive a one year PT program according the standardized PT program in combination with BTX injections. The PT program will start two weeks after the injections. The emphasis of the PT program is on the functional performance of the exercises adapted to daily life situations, muscle stretching, passive mobilization of the neck and training principles which have found to be relevant for neural rehabilitation and motor learning and will be performed by trained physical therapists [18-20]. A summary of the theoretical basis with respect to *‘muscle stretching and mobilizations’ , ‘motor (re)learning’, ‘transference and generalization’, ‘feedback’ and ‘self management’,* is displayed in Table 1.

#### Regular PT

Subjects randomized in this group will receive BTX injections and regular PT once a week for a period of one year. In contrast to the standardized PT program, interventions are not given by specialized therapists. Due to the rarity of CD, the average therapist in the Netherlands has little knowledge about CD. It is likely that common interventions like massage, stretching and exercise of the dystonic muscles are used. Specific information of the weekly sessions and treatment will be retrieved from the local PT’s after the patients finished the study period of one year.

### Outcome variables

#### Disability

Disability as measured with the disability subscale of the Toronto Western Spasmodic Torticollis Rating Scale (TWSTRS) is the primary outcome of this study. The TWSTRS scale is a widely used scale in research and is a valid and reliable tool to measure severity, disability and pain in CD (Kendall Tau = 0.85, p < 0.01) [23,24]. The disability section is a six point Likert scale which consists of six items like driving a car, reading and performing ADL activities (max 30 points). Lower scores indicate less disability.

Disability will also be measured with the Functional Disability Questionnaire (FDQ). The FDQ is a 27 item scale to measures the impact of CD on daily functioning. Questions are asked about the extent to which CD affects the engagement in and performance of a sample of activities at the present time. Each item is rated on a 5-point scale (maximal score 68 points) The FDQ has a high reliability (r=.93, P<0.001) [25].

#### Severity of CD

Severity of CD will be measured with the Tsui scale [26]. The Tsui scale measures different aspects of abnormal posture and movements in CD patients. It has a maximal score of 25 points. The Tsui-scale is a widely used, standardized and reliable scale (ICC=.86) to measure the severity of CD [26] Lower scores indicate less severity of dystonia.

Severity of CD will also be measured with the Clinical Global Impressions-Severity of Illness Scale (CGI-S) and the Clinical Global Impression - Improvement scale (CGI-I). Both scales are observer- or patient- rated scale that measure illness severity and global improvement on a 7-point scale. Both scales are widely used and reliable and validated for a numerous of disorders (r=0.41 to 0.77, p=0,05 for self perceived measures and r=0.36 to 0.84, p=0.05 of clinician administered measures of anxiety, depression, impairment and quality of life) [27,28].

#### Active range of motion

To determine the changes in the ability to perform voluntary movements, active range of motion (AROM) will be measured with a cervical range of motion meter (CROM) [29]. The CROM is a frame that will be placed on the head with three separate inclinometers to measure AROM in the sagittal, coronal and horizontal planes. First the resting position of the head will be measured and subsequently the AROM of flexion, extension, lateral flexion and rotation. Although the psychometric properties of the CROM in patients with CD are unknown, in a healthy population the CROM is a reliable instrument to measure cervical ROM (intratester reliability ranged .63-.93 intertester reliability ranged .74 -.87) [29]. To determine the additional effects of PT on pain, patient are asked to rate their pain on a Numeric Rating Scale (NRS). A score of 0 means no pain and a score of 10 means the worst pain imaginable. The NRS is a validated and reliable tool for the assessment of pain (Spearman r =.94 between VAS and NRS, test-retest reliability ICC = .90) [30,31].

#### Quality of life

Quality of Life (QoL) will be measured with the Cranio-cervical Dystonia Questionnaire (CDQ-24) and Short Form 36 (SF-36) [32,33]. The CDQ-24 is a validated and disease specific, self reporting questionnaire to evaluate quality of life of patients with cervical dystonia on a five point likert scale [32]. The CDQ-24 subscales showed moderate to high correlations with those SF-36 subscales measuring similar aspects (Pearson’s correlation r = 0.50–0.73; P<0.001, each).The score ranges from 0 to 96 points where lower scores indicate a better QoL. The SF-36 is a validated generic measure for QoL containing 36 items measuring eight dimensions of health [33]. Scores of the different dimensions can range from 0 (worst) to 100 (best).

#### Anxiety and depression

Since 25 to 59% of the CD patients suffer from anxiety disorders or depression [25,34], the effects of PT are determined with the Beck’s Anxiety Index [35] and Beck’s Depression Index [36,37]. Both instruments are validated and reliable tools and are rated on a 21 item 4 point Likert scale (BDI: r = .73 with Hamilton Psychiatric Rating Scale for Depression. BAI: test-retest reliability coefficient of .67, R=.54, p=0.05 with anxiety).

#### Cost effectiveness

To determine the cost effectiveness of both physical therapy programs, the costs per quality adjusted life year (QALY) will be calculated. In addition, cost-effectiveness related to the clinical outcome will be calculated, with the costs per unit on the TWSTRS-disability scale as the outcome measure. Costs which are associated with loss of productivity due to disability or inability to work will be registered in the subgroup of patients below the age of 65 with the Productivity Costs Questionnaire (PCQ) and EuroQoL-5D (EQ-5D). The PCQ is a 22 item generic questionnaire used to measure absence of work due to health problems and is advised as standard instrument for use in economic evaluations of Dutch healthcare [38,39]. The EQ-5D is a six item, standardized measure of health status in order to provide a simple, generic measure of health for clinical and economic appraisal [39,40].

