**Methods/design:**

The (cost-) effectiveness of a standardized physical therapy program compared to regular physical therapy, both as add-on treatment to botulinum toxin injections will be determined in a multi-centre, single blinded randomized controlled trial with 100 cervical dystonia patients. Primary outcomes are disability in daily functioning assessed with the disability subscale of the Toronto Western Spasmodic Torticollis Rating Scale. Secondary outcomes are pain, severity of dystonia, active range of motion of the head, quality of life, anxiety and depression. Data will be collected at baseline, after six months and one year by an independent blind assessor just prior to botulinum toxin injections. For the cost effectiveness, an additional economic evaluation will be performed with the costs per quality adjusted life-year as primary outcome parameter.

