### Analysis

Differences in all outcome measures, with exception of the measures for cost effectiveness, will be determined with a mixed between-within (repeated measures) analysis of variance for both treatment arms, across three time periods (baseline, after six months and one year). All analyses will be performed under the intention to treat principle in SPSS 20.0. Differences will be considered significant at p-value < 0.05.

The cost effectiveness will be determined by a cost-utility analysis from a societal perspective with a time horizon of one year. Cost-utility analysis facilitates the comparative assessment of health care innovations across different types of interventions, disease areas and health care settings. Incremental cost-utility and cost-effectiveness ratios for the add-on standardized PT program versus add-on regular PT will be calculated as the extra costs per QALY gained and the extra costs per unit decrease in TWSTRS-disability score. The cost effectiveness will be calculated according the most recent guidelines for unit costing in healthcare research [40]. The friction cost method will be applied to calculate the costs of production loss as measured with the PCQ, EQ-5D. Unit costs of production loss will be based on the most recent national guidelines for unit costing in healthcare research [40]. The base year for unit costing will be 2013.

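### The article assigns the EQ-5D to productivity costs in patients under 65, so, read literally, the cost-per-QALY comparison does not cover the randomised population

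*Protocol article*

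**What the plan says.** The abstract of the protocol article announces that "an additional economic evaluation will be performed with the costs per quality adjusted life-year as primary outcome parameter". Under Outcome variables, Cost effectiveness, the paragraph opens by repeating that "the costs per quality adjusted life year (QALY) will be calculated", without naming an instrument. It then turns to costs from lost productivity, which "will be registered in the subgroup of patients below the age of 65 with the Productivity Costs Questionnaire (PCQ) and EuroQoL-5D (EQ-5D"). The same paragraph then describes the instrument in general terms, as one meant for appraisal: "The EQ-5D is a six item, standardized measure of health status in order to provide a simple, generic measure of health for clinical and economic" …

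The Analysis section states: "The cost effectiveness will be determined by a cost-utility analysis from a societal perspective with a time horizon of one year". It plans incremental ratios for QALYs and for the TWSTRS disability score, and neither carries an age restriction. On production loss it says: "The friction cost method will be applied to calculate the costs of production loss as measured with the PCQ, EQ-5D".

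The Participants section aims for "100 patients with primary CD of 30 years and older" and sets no upper age limit. The Quality of life section lists the SF-36, also without an age limit, as a quality-of-life outcome scored by dimension.

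**The concern.** Two things do not fit together.

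- **Purpose.** The EQ-5D is described as a measure of health status, but both places that give it a job use it for production loss. Neither links it to QALYs.
- **Population.** The one sentence on its collection places it, with the PCQ, in the subgroup below 65. An age limit of that kind suits work absence. It does not suit the health utilities of a trial that also enrols older patients.

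The primary economic parameter needs a utility for every randomised patient. A site that followed the wording would not hand the EQ-5D to a patient of 70. The QALY difference would then come from an age subgroup that nobody planned, while the companion ratio per TWSTRS disability point would rest on all patients. EQ-5D answers not collected at baseline or six months cannot be collected afterwards.

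**Working it through.** The plan states no figure on this point, so there is none to reproduce. The check is a comparison of every place that mentions the EQ-5D, QALYs, the SF-36 or age, followed by an illustration of size.

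**Step 1: set the statements side by side.**

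| Element | Where | What is stated | Age limit |
|---|---|---|---|
| Eligibility | Participants | from 30 years | no upper limit |
| Primary economic parameter | Abstract, Methods/design | cost per QALY | none |
| Cost-utility analysis | Analysis | extra cost per QALY gained | none |
| EQ-5D, collection | Cost effectiveness | with the PCQ, for productivity costs | below 65 |
| EQ-5D, description | Cost effectiveness | generic health-status measure | none stated |
| EQ-5D, use | Analysis | production loss, friction cost method | none stated |
| SF-36 | Quality of life | quality-of-life outcome, no utility conversion | none |

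**Step 2: look for a utility source.** A QALY needs a utility. The EQ-5D is the only health-status instrument in the economic section, and its stated use is production loss. The SF-36 is given no role in the economic evaluation. So no instrument is named as the utility source at any age, and for patients of 65 and older the only candidate in the economic section is, on the literal wording, not collected.

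**Step 3: size under an assumed share.** Let s be the proportion aged 65 or older. The article does not give it, so 10% to 40% is assumed purely for illustration. Further assumptions are 100 patients split 50 and 50, the same s in both arms, and the same QALY variance with and without the older patients.

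- Patients without an EQ-5D = 100 × s
- Patients with an EQ-5D per arm = 50 × (1 − s)
- Standard error factor for the QALY difference = 1/√(1 − s)

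| Assumed s | Without EQ-5D | With EQ-5D per arm | SE factor |
|---|---|---|---|
| 10% | 10 | 45 | 1/√0.90 = 1.05 |
| 20% | 20 | 40 | 1/√0.80 = 1.12 |
| 30% | 30 | 35 | 1/√0.70 = 1.20 |
| 40% | 40 | 30 | 1/√0.60 = 1.29 |

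The plan's 10% allowance for loss would multiply each count per arm by 0.9 (for example 40 × 0.9 = 36). It leaves the factor unchanged if loss is equal across ages. The factor describes lost precision only. It does not capture the larger problem, that the QALY difference would apply to patients under 65 rather than to those randomised.

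**The case against.** The strongest reply is that this is a compressed sentence. Its grammatical subject is productivity costs, for which a limit at 65 is natural, and nothing says that the EQ-5D is withheld from older patients. The paragraph opens with cost per QALY for both programmes, the EQ-5D is described as suited to economic appraisal, and the Study design section schedules all data at the three assessments. The friction-cost sentence repeats the link to production loss but not the age limit. An article may also leave the value set and the QALY calculation to a fuller document.

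Much of this stands. The age limit does rest on one sentence, and the authors may have meant the PCQ for those under 65 and the EQ-5D for everyone. The text does not say so, however. The wrong purpose appears in two sections, and a stated misassignment is different from a detail left out for brevity.

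Two stronger readings are tempting, and the article does not support them.

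- A reader might infer that QALYs cannot be computed at all for patients of 65 and older. The SF-36 is collected without an age limit and could in principle be converted to a utility. What holds is that no such conversion is stated.
- A reader might infer that the ratio would set costs from all patients against QALYs from those under 65. The article does not say in whom costs other than productivity costs are collected, so a mismatch on the cost side cannot be shown.

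**Conclusion.** The point holds as a faulty assignment in the text. The EQ-5D is given to production loss in two sections and, in the only sentence on its collection, to patients below 65. No instrument is named as the utility source for a cost-utility analysis that has no age restriction. If the wording is followed, patients of 65 and older have no EQ-5D data and the QALY comparison does not cover the randomised population.

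The number of patients affected is unknown. The precision loss of about 1.12 to 1.29 depends on the literal reading and on an assumed 20% to 40% aged 65 or older. Severity is moderate: the defect touches the primary parameter of the economic evaluation and the lost data could not be collected later, but the primary clinical outcome, its sample size and its analysis are not affected.

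**What to change.** Make three wording changes.

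1. In Cost effectiveness, state that all randomised patients, whatever their age, complete the EQ-5D at baseline, six months and one year, and that it is the source of utilities for the QALYs.
2. In the same paragraph, apply the under-65 restriction to the PCQ alone.
3. In Analysis, delete the EQ-5D from the friction-cost sentence, so that production loss rests on the PCQ.

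The cost is a six-item questionnaire for older patients at assessments they already attend. Under the assumed 20 to 40 such patients, that is 20 × 3 = 60 to 40 × 3 = 120 extra forms over the trial, before any drop-out. If the sites already give the EQ-5D to everyone, only the text has to change.

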### Sample size

The power calculation is based on the study by Brans et al. investigating the long term effect of BTX on disability and functional health [41]. This study showed an average improvement of 7.1 out of 30 points on the disability subscale of the TWSTRS after 1 year of BTX treatment in CD patients. It is estimated that the additional effect of the PT program according the treatment guideline will be at least half the effect caused by BTX. The cut off for the success of the PT program is therefore, set on an average improvement of 3.5 out of 30 points on the TWSTRS disability scale which is clinically relevant according Brans et al. [42]. With a power of 0.80 and an alpha of 0.05, each group will need 44 subjects. With a loss of 10% taken into account, 50 subjects in each group are required.

### Analysis

Differences in all outcome measures, with exception of the measures for cost effectiveness, will be determined with a mixed between-within (repeated measures) analysis of variance for both treatment arms, across three time periods (baseline, after six months and one year). All analyses will be performed under the intention to treat principle in SPSS 20.0. Differences will be considered significant at p-value < 0.05.

The cost effectiveness will be determined by a cost-utility analysis from a societal perspective with a time horizon of one year. Cost-utility analysis facilitates the comparative assessment of health care innovations across different types of interventions, disease areas and health care settings. Incremental cost-utility and cost-effectiveness ratios for the add-on standardized PT program versus add-on regular PT will be calculated as the extra costs per QALY gained and the extra costs per unit decrease in TWSTRS-disability score. The cost effectiveness will be calculated according the most recent guidelines for unit costing in healthcare research [40]. The friction cost method will be applied to calculate the costs of production loss as measured with the PCQ, EQ-5D. Unit costs of production loss will be based on the most recent national guidelines for unit costing in healthcare research [40]. The base year for unit costing will be 2013.

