**Self management (Fitts** &**Posner three-stage model**[48]**)**		
*Principle*	*Explanation*	*Application in standardized PT program*
1. Cognitive phase	The learner is concerned with understanding a task and developing strategies to perform a task and how the task can be evaluated. These efforts require a high degree of cognitive activity	During the first month patients receive 2 PT sessions a week to (re)learn and understand movement strategies. Movement strategies will be practiced at home 5–10 times a day for 10–15 minutes
2. Associative phase	The learner has selected the best strategy for a task and starts to refine it. This stage requires less cognitive activity	During this stage patients receive 1 PT session. Movement strategies from the first stage will be increased in difficulty. Movement strategies will be practiced at home 5–10 times day for 10–15 minutes
3. Autonomous phase	The learner is able to perform a skill automatically. A low degree of attention is required.	During the last (autonomous) stage, patients are encouraged to perform the learned tasks independently and to improve and maintain their (re)gained abilities themselves. Therapists will have a coaching role. Patients receive one PT session a month for additional advice and motivation.

The primary objective of this study is to evaluate the effectiveness of the standardized PT program on improving the ability to perform daily life activities in CD patients compared to usual PT that is given in Dutch private practices. Both PT programs are add-on treatment to BTX-injections. Measurement will take place just prior to the BTX injections as it is hypothesized that the effects of the PT program will mainly occur in the period between the injections when the BTX wears off and symptoms return (Figure 1). Secondary objectives are to evaluate the effects on severity of CD pain, quality of life, anxiety and depression.

In addition, cost effectiveness will be detremined by comparing the costs and health utility of the new standardized PT program with the care as usual PT treatment. It is hypothesized that the standardized PT program will be more cost effective and more effective in improving the ability to perform daily life tasks of CD patients than regular PT.

A positive outcome of this study will lead to the development of a national treatment guideline which will be implemented via the Dutch DystonieNet.

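### The planned three-visit ANOVA counts baseline as an outcome level and names no deciding term, and neither of its arm tests is the between-arm difference after the one-year programme

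*Protocol article*

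**What the plan says.** - **Outcome** (Protocol article, first subsection on the outcome measures): "Disability as measured with the disability subscale of the Toronto Western Spasmodic Torticollis Rating Scale (TWSTRS) is the primary outcome of this study". No visit is attached to it.
- **Objective** (end of Background): the programme is judged on "improving the ability to perform daily life activities in CD patients compared to usual PT that is given in Dutch private practices", which is a between-arm question.
- **Analysis**: all outcomes except the cost measures are compared by a "mixed between-within (repeated measures) analysis of variance for both treatment arms, across three time periods (baseline, after six months and one year"). Baseline is therefore one of three levels of the outcome factor. The only decision rule is "Differences will be considered significant at p-value < 0.05". No term, visit or contrast is named, and baseline is not used as a covariate anywhere in the article.
- **Sample size**: the anchor is an earlier botulinum toxin (BTX) study, in which patients gained a mean of 7.1 points on this 30-point subscale over one year. The section then assumes that "the additional effect of the PT program according the treatment guideline will be at least half the effect caused by BTX", and the target is "set on an average improvement of 3.5 out of 30 points on the TWSTRS disability scale". The result is "With a power of 0.80 and an alpha of 0.05, each group will need 44 subjects", raised to 50 for 10% loss.

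**The concern.** The sample size describes one comparison of two means. The stated analysis yields two different tests that involve the arm: a main effect averaged over all three visits, and an arm-by-time interaction with 2 degrees of freedom. The plan does not say which of them decides.

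The main effect includes a visit taken before treatment, so it is diluted by design. The interaction asks whether the arms differ in their course over time, but not in which direction or at which visit.

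The Discussion section justifies a full year of treatment by the wish for lasting change. The Future implications section makes a positive result the basis of a national guideline. A test that can be positive on a six-month difference that has gone by one year is a weak foundation for that step.

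**Working it through.** **Inputs.** From the Sample size section: difference 3.5 points (half of 7.1 is 3.55, taken as 3.5), power 0.80, alpha 0.05, 44 per group. From Study design: visits at baseline, six months and one year. The article gives neither an SD nor a between-visit correlation ρ. The SD is therefore solved from the stated sample size, and ρ is assumed to lie between 0.3 and 0.8 with compound symmetry.

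**The plan's own figure.** With no SD stated, the 44 cannot be reproduced directly. Solving the two-sided normal formula backwards gives SD = 3.5 × √(44/2) / (1.960 + 0.842) = 16.42 / 2.802 = 5.86. Using 43 in place of 44 gives 5.79, so any SD in this range rounds up to 44. An exact two-sample t test with 44 per group has 80% power at SD 5.79, which is used below. If alpha was meant one-sided, the implied SD is 6.53 to 6.60. The loss allowance gives 44 / 0.9 = 48.9, so 50 per group is consistent.

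**Arm main effect.** The estimate is the mean of the three visit differences, and the SD of a patient's mean is SD × √((1 + 2ρ)/3). With 3.5 at both follow-ups the estimate is (0 + 3.5 + 3.5)/3 = 2.33. At ρ = 0.5 the SD of the mean is 5.79 × √(2/3) = 4.73 and the standard error is 4.73 × √(2/44) = 1.01. The ratio 2.33 / 1.01 is about 2.31, and power is 63%.

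**Arm-by-time test.** This is a noncentral F with 2 and 2 × (88 − 2) = 172 df, and λ = (44/2) × Σ(δ − mean δ)² / (SD² × (1 − ρ)). For differences of (0, 3.5, 3.5) the sum of squares is 5.44 + 1.36 + 1.36 = 8.17. For (0, 0, 3.5) and (0, 3.5, 0) it is 1.36 + 1.36 + 5.44, again 8.17. The three profiles therefore share the same λ and the same power. At ρ = 0.5, λ = 22 × 8.17 / (33.6 × 0.5) ≈ 10.7 and power is 84%.

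**One-year difference adjusted for baseline.** The residual SD is SD × √(1 − ρ²). At ρ = 0.5 this is 5.02, the standard error is 1.07, the ratio is 3.27, and power is 90%.

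Power (%) at ρ = 0.3 / 0.5 / 0.7 / 0.8:

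| True difference at baseline, 6 months, 1 year | Average over visits | Arm main effect | Arm-by-time, 2 df | One-year, baseline-adjusted |
|---|---|---|---|---|
| 0, 3.5, 3.5 | 2.33 | 73 / 63 / 55 / 52 | 69 / 84 / 97 / 99.8 | 84 / 90 / 98 / 99.7 |
| 0, 1.75, 3.5 | 1.75 | 48 / 40 / 35 / 33 | 56 / 71 / 91 / 98 | 84 / 90 / 98 / 99.7 |
| 0, 0, 3.5 | 1.17 | 25 / 21 / 18 / 17 | 69 / 84 / 97 / 99.8 | 84 / 90 / 98 / 99.7 |
| 0, 3.5, 0 | 1.17 | 25 / 21 / 18 / 17 | 69 / 84 / 97 / 99.8 | 5 at every ρ |

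The last row is the key one. With no difference left at one year, the interaction rejects exactly as often as when the full difference is present at one year. The baseline-adjusted one-year test stays at its 5% level.

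**The case against.** The strongest defence is that arm-by-time is the usual efficacy term in such a design. It is valid under randomisation, and it does use baseline, through within-patient change. For the full effect at both follow-ups its power is 84-97% at ρ 0.5-0.7, above the planned 80%. All of that stands. A reader might infer from the diluted main effect that the trial is underpowered. The article does not support this, because it never says that the main effect decides, and the interaction falls short for that profile only at low correlation (69% at 0.3).

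A reader might also infer that the type I error is about 10%. Accepting either arm term at 0.05 would give 1 − 0.95² = 9.75% if the two tests are treated as independent. But the article states no either-test rule. It merely leaves the choice open.

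Third, the Sample size section does not literally call the 3.5 points a one-year between-arm difference. The one-year period belongs to the BTX study used as anchor, and the article ranks neither follow-up visit above the other. The one-year between-arm reading is an inference from the additional effect, the per-group number, the one-year programme and the stated wish for lasting change. It is the natural reading, but it remains an inference.

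Finally, contrasts are often left to an analysis plan, and none is shown here. That excuses missing detail. It does not remove the point, because the article positively fixes a model with baseline among the outcome visits.

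**Conclusion.** The point holds as an unspecific decision test, not as a demonstrated loss of power or a demonstrated inflation of error. The stated model offers two arm tests. One shrinks a 3.5-point effect at both follow-ups to 2.33, and its power stays below 80% across ρ 0.3-0.8 (73% down to 52%). The other is valid and often well powered, but it cannot separate a benefit present at one year from one present only at six months. Neither is the comparison that the 44 per group most naturally describes.

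The dilution to 2.33 and the equal interaction power of the three profiles do not depend on the SD. The power figures do depend on the back-solved SD of 5.79, on compound symmetry and on the assumed correlations. This should be fixed, but it does not invalidate the design.

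**What to change.** Name a single primary test in the Analysis section: the between-arm difference in TWSTRS disability at one year, adjusted for baseline TWSTRS disability, two-sided at 0.05, reported with a 95% confidence interval. It can come from an ANCOVA, or from a linear mixed model on the two follow-up visits with arm-by-visit and baseline terms. Make the six-month difference secondary. State that neither the ANOVA main effect nor the omnibus arm-by-time test serves as the test of efficacy. Settle this before any data are seen by arm.

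The cost is a change of wording. All the measurements are already scheduled and no further patients are needed.

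### The named repeated-measures ANOVA drops every patient with a missing visit, so as written it cannot deliver the stated intention-to-treat analysis

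*Protocol article*

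**What the plan says.** In the Analysis section, every clinical outcome, including the primary TWSTRS disability score, "will be determined with a mixed between-within (repeated measures) analysis of variance for both treatment arms". The visits that enter this model are listed there as well: baseline, month 6 and month 12. The next sentence reads "All analyses will be performed under the intention to treat principle in SPSS 20.0". The section names no imputation, no likelihood-based model and no other handling of incomplete patients.

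The Sample size section states "With a power of 0.80 and an alpha of 0.05, each group will need 44 subjects". It then inflates that number for expected dropout: "With a loss of 10% taken into account, 50 subjects in each group are required". Missing data are therefore expected, and lost patients are budgeted as contributing nothing.

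Three other places bear on who might be lost. The Study design section says that patients and therapists cannot be blinded. In Table 1 (Self management), the experimental arm's home training in the first two phases is described as "Movement strategies will be practiced at home 5–10 times a day for 10–15 minutes" or in near-identical words. The Regular PT section gives the control arm weekly sessions for a year and mentions no home programme.

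**The concern.** A classical between-within ANOVA, which SPSS runs as its repeated-measures GLM procedure, works on patients with a complete row of scores and deletes the rest list-wise. With three visits in the model, one missing visit removes the patient from all of them. The word mixed does not help: here it means one between-patient factor (arm) and one within-patient factor (visit), not a linear mixed model.

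Two adjacent sentences therefore pull apart. One promises an analysis of patients as randomised; the other names a procedure that, without a further step, analyses completers. At stake are the 12-month scores thrown away because a 6-month score is absent, and a possible bias if the reason for missing a visit is related to response and differs by arm. The second is possible here because patients know their allocation and the arms ask different things of them: home practice of 5 × 10 = 50 to 10 × 15 = 150 minutes a day in the early phases, against weekly sessions.

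**Working it through.** **Inputs from the article.** 44 needed per arm, 10% loss, 50 per arm, target difference 3.5 points, alpha 0.05, power 0.80, three visits.

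**Inputs assumed, because the article does not give them.** SD, correlation between visits, dropout rule, loss by arm, and a two-sided test.

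**1. The plan's own figure.** 44 / 0.9 = 48.9, so 49; the stated 50 agrees within rounding. The 44 cannot be checked directly because no SD is reported. Solving n = 2(1.96 + 0.842)² SD² / 3.5² for n = 44 gives an SD of about 5.80 to 5.85.

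**2. Patients removed at the planned loss.** 100 × 0.10 = 10, leaving 50 × 0.9 = 45 complete cases per arm.

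**3. Power.** Power = Φ(3.5 / (SD √(2/n)) − 1.96), with SD 5.80 to 5.85:

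| Complete cases per arm | Power |
|---|---|
| 50 | 0.85 |
| 45 (planned 10% loss) | 0.81 to 0.82 |
| 44 (required) | 0.80 to 0.81 |
| 40.5 (a further 10% miss month 6: 50 × 0.9 × 0.9) | 0.77 |

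Only the last row falls below the requirement, and its 6-month rate is an assumption.

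**4. Bias in 12-month change with no true effect.** Assume SD 5.8 and correlation 0.6 between any two visits. The SD of change is 5.8 × √(2 × 0.4) = 5.19, and the 6- and 12-month changes correlate at 0.5. Control loss is 5%, unrelated to response. In the experimental arm a fraction h of patients without 6-month improvement is lost, and a fraction l of those with improvement. The completers' mean change then shifts by

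0.5 × 5.19 × 0.798 × (l − h) / (2 − h − l) = 2.07 × (l − h) / (2 − h − l).

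| Rule in the experimental arm | Overall loss there | Shift in favour of the programme |
|---|---|---|
| h = 0.13, l = 0.05 | 9% | 2.07 × 0.08 / 1.82 = 0.09 |
| h = 0.21, l = 0.05 | 13% | 2.07 × 0.16 / 1.74 = 0.19 |
| h = 0.26, l = 0 | 13% | 2.07 × 0.26 / 1.74 = 0.31 |
| Logistic in 6-month change, log-odds slope 1.5 per SD (simulated) | 13% | 0.40 |
| Logistic, slope 2 per SD (simulated) | 13% | 0.46 |

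The range is roughly 0.1 to 0.5 points. For scale, the standard error of the difference in change at 44 per arm is 5.19 × √(2/44) = 1.1.

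**5. The same question with a true effect of 3.5** (SD 5.85; effect 1.75 at 6 months; loss after month 6; large-sample simulation). Full data and the all-visits estimate both recovered 3.5 within simulation error. Completers gave:
- 3.5 when 10% loss was unrelated to response;
- 3.30 to 3.44 when one response-related rule applied to both arms, at 10% to 20% overall loss and correlations 0.4 to 0.8;
- 3.97 to 4.23 when, at 10% loss per arm, poor responders left the experimental arm and good responders left control.

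The all-visits estimate in steps 4 and 5 was a regression prediction valid under missing at random, standing in for the likelihood model. In step 4 its bias was about zero.

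**The case against.** The conflict is inferred. The article nowhere says that incomplete patients are excluded, and intention to treat is compatible with this ANOVA if missing scores are imputed first. A fuller protocol or SAP may say so. That is fair, and it would resolve the point. But the article does more than stay silent: it fixes a procedure, and that procedure as named cannot keep the patients the stated principle requires.

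Stopping therapy is not the same as missing an assessment. Scores are taken at the hospital clinic just before injections that both arms continue, by patients already stable on that treatment for over a year. Someone who abandons the exercises still has reason to attend, and nothing in the article says assessment ends with therapy. This stands, and it weakens the link between training burden and missing scores.

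A reader might infer that the completers analysis will favour the new programme. The article does not support that. It gives no loss by arm and no reasons for loss. The heavy home load is stated for the first two phases, with the last falling to one session a month, while controls attend weekly all year. Burden could cause loss in either arm, and under a common rule the bias runs toward no effect.

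A reader might also infer that the trial becomes underpowered. The plan already budgets for the 10% loss, and 45 exceeds 44.

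**Conclusion.** The point holds as a mismatch between method and principle. Following the Analysis section as written yields a completers analysis under an intention-to-treat label, with about 10 of 100 randomised patients left out at the plan's own loss rate. That conclusion needs no simulation; it rests on how the named ANOVA treats incomplete rows and on the absence of a stated remedy.

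The bias is conditional in size and in direction. The 0.1 to 0.5 points toward the programme (about 3% to 14% of the 3.5 target: 0.1/3.5 and 0.5/3.5) assumes that poor responders leave mainly the experimental arm, with SD 5.8, correlation 0.6, 9% to 13% experimental loss and 5% control loss. Values near 0.4 or above need a steep graded rule. The larger shifts in step 5 need opposite dropout patterns in the two arms, for which the article offers no evidence. The loss of power is minor unless a sizeable further group misses the 6-month visit.

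**What to change.** Replace the ANOVA in the Analysis section with a likelihood-based linear mixed model (SPSS MIXED), with arm, visit and arm-by-visit terms. Use all available scores of all randomised patients in their allocated arm, and take the 12-month arm contrast from the model. A patient with a baseline and a 12-month score then counts toward the primary comparison, and one lost after month 6 contributes the scores that exist. Multiple imputation before the named ANOVA is an acceptable alternative if the authors wish to keep it; the article should then say so.

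Both options assume that missingness depends only on observed data. A missing-not-at-random sensitivity analysis would probe that and is optional.

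The cost is a few lines of wording and slightly more analysis work in the same software. No extra patients or visits are needed, and the sample size is unaffected. The change should be made before the data are analysed, because it governs the primary result.
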